## Abstract

**Background:**

Pulmonary rehabilitation (PR) is effective for improving symptoms and functional status in patients with chronic obstructive pulmonary disease (COPD), particularly respiratory training. However, its effectiveness is often compromised by poor adherence. Music therapy has increasingly being applied to COPD PR, due to its safety, low cost, and potential to motivate and enhance participation. Therefore, an integrated intervention combining music-guided breathing training and singing may represent a more appealing alternative rehabilitation strategy. This study protocol aims to evaluate whether this music-based integrated intervention is non-inferior to conventional PR therapy in terms of functional mobility, adherence and other patient-centered outcomes will be assessed as secondary or exploratory outcomes.

**Methods:**

This is a multicenter, double-arm, parallel-group, randomized controlled non-inferiority trial. We plan to recruit 76 patients with stable moderate-to-severe COPD, and randomize them in a 1:1 ratio to either the Music Therapy group (MTG) or the Conventional Pulmonary Rehabilitation group (CPRG). The MTG will receive music-guided breathing exercises and singing; the CPRG will receive non-music-guided breathing exercises and aerobic exercise. Both groups undergo interventions at a frequency of 60 min per session, 3 times per week, for 6 weeks. The primary outcome is the between-group difference in change in the 6-min walk distance (6MWD) from baseline to week 6, assessed under a non-inferiority framework. Key secondary outcomes include dyspnea severity, respiratory health status, pulmonary function, and adherence-related measures. Exploratory outcomes include arterial blood gas parameters, Traditional Chinese Medicine (TCM) syndrome assessment, patient satisfaction, safety, and the number of acute exacerbations of COPD (AECOPD) during the 1-year post-intervention follow-up. This trial protocol has been approved by the ethics committees of all participating centers.

**Discussion:**

This study aims to evaluate whether an integrated rehabilitation intervention of music-guided breathing training and singing is non-inferior to conventional PR in terms of functional outcomes for patients with COPD. Secondary outcomes, including adherence, feasibility, and patient-reported measures, will be assessed as secondary or exploratory outcomes and interpreted cautiously. The findings may help inform the development of alternative rehabilitation strategies for this population.

**Clinical trial registration:**

https://itmctr.ccebtcm.org.cn, identifier ITMCTR2026000211.

## Introduction

1

Chronic obstructive pulmonary disease (COPD) is a chronic respiratory disorder characterized by persistent respiratory symptoms and airflow limitation. Its high prevalence and mortality rates, prolonged treatment cycles, and recurrent acute exacerbations impose a significant burden on public health systems worldwide (1). Therefore, the management goal for stable-phase COPD is to alleviate symptoms and reduce the occurrence of acute exacerbations. Pulmonary rehabilitation (PR) is recognized as a vital therapeutic approach for COPD, aimed at enhancing respiratory muscle strength, alleviating respiratory symptoms, improving physical activity tolerance, reducing complications, and enhancing quality of life in COPD patients (2–4). However, patient compliance remains low, making long-term adherence challenging and ultimately limiting therapeutic outcomes (5). Consequently, identifying engaging interventions that effectively integrate core rehabilitation principles has emerged as a key research focus.

Breathing exercises are an important component of pulmonary rehabilitation for patients with COPD, helping to improve breathing patterns, ventilatory efficiency, and respiratory muscle function (6–8). Meanwhile, the use of singing-based interventions for chronic respiratory diseases has gradually garnered attention. During singing, rapid inhalation and prolonged exhalation require coordinated activation of the diaphragm and expiratory muscles (9). Previous studies have shown that singing-based training can produce respiratory muscle training effects in patients with COPD comparable to those of conventional breathing exercises (8). Furthermore, singing-based and other music-related interventions may help improve self-reported symptoms, exercise capacity, mental health, and treatment adherence in patients with COPD (10–14).

Music can also promote rehabilitation through rhythmic cues and emotional support. Musical rhythms serve as external rhythmic cues that help regulate breathing patterns, while the enjoyment and engaging nature of music itself can also enhance patients’ motivation and engagement during repetitive training sessions. Some studies suggest that the rhythm or melody also may be a potential mechanism for alleviating breathlessness and fatigue during exercise (15). Overall, these findings provide a theoretical basis for integrating breathing training, musical cues, and singing tasks into a unified rehabilitation model, rather than treating them as separate intervention components.

Based on the above considerations, the intervention proposed in this study was designed as an integrated rehabilitation model that uses musical rhythms to assist with breath control and employs vocalization and singing exercises to train patients to prolong exhalation and coordinate breathing with vocalization. This integrated model provides a structured rehabilitation approach for patients with COPD.

Although breathing exercises, music-assisted rehabilitation, and singing interventions have each been explored to some extent among patients with chronic respiratory diseases, evidence regarding the integration of combining music-guided breathing training with singing into a structured COPD rehabilitation model remains limited. In particular, it is unclear whether such music-based integrated strategies can achieve outcomes that are non-inferior to those of conventional pulmonary rehabilitation in terms of functional outcomes.

Consequently, this randomized controlled trial aims to evaluate the efficacy of music-guided breathing training combined with singing intervention in patients with COPD. The primary objective of this study is to assess whether this integrated intervention is non-inferior to traditional pulmonary rehabilitation training in improving the 6-min walk distance. Secondary objectives include exploring its effects on lung function, dyspnea, symptom burden, patient-reported outcomes, adherence, satisfaction, and the frequency of acute exacerbations during follow-up.

## Methods and analysis

2

### Study design

2.1

This trial is a prospective, multicenter, double-arm, assessor-blinded, parallel-group, randomized controlled non-inferioritytrial. Eligible participants will be randomized 1:1 to either Music Therapy Group (MTG) or Conventional Pulmonary Rehabilitation Group (CPRG). Both groups will receive interventions at a frequency of 60 min per session, 3 times per week, for 6 weeks.

The primary outcome is the between-group difference change in the 6-min walk distance (6MWD) from baseline (T0) to Week 6 (T6), which will be evaluated under a non-inferiority framework. Non-primary outcomes include dyspnea severity, respiratory health status, pulmonary function, adherence-related measures, arterial blood gas parameters, Traditional Chinese Medicine (TCM) syndrome assessment, patient satisfaction, adverse events, and the number of acute exacerbations of COPD (AECOPD) during the 1-year post-intervention follow-up.

The 6MWD, the COPD Assessment Test (CAT), and the modified Medical Research Council (mMRC) dyspnea scale will be measured at baseline (T0), weekly during the intervention (T1–T5), and post-intervention (T6). Pulmonary function and arterial blood gas analysis will be measured at T0 and T6. Adherence-related measures and adverse events will be recorded throughout the intervention period. AECOPD outcomes will be recorded throughout the 1-year follow-up. This study will adhere to the Consolidated Standards of Reporting Trials (CONSORT) statement for non-drug trials. The trial flowchart is shown in Figure 1, and assessment plan for primary and secondary outcome measures is shown in Table 1.

**Figure 1 fig1:**
[figure not shown]
Study flowchart showing participant screening, randomization, intervention allocation, and follow-up.

**Table 1 tab1:** Assessment plan for primary and secondary outcome measures.

Outcomes	Time points	Measurement tools and methods
Primary outcome		
Exercise capacity	T0, T1, T2, T3, T4, T5, T6	6-min walk test (6MWT)
Secondary outcomes		
Key secondary outcomes		
Dyspnea severity	T0, T1, T2, T3, T4, T5, T6	mMRC score, modified Borg dyspnea scale
respiratory health status	T0, T1, T2, T3, T4, T5, T6	CAT score
pulmonary function	T0, T6	FEV_1_, FVC, and the FEV_1_/FVC ratio
adherence-related outcomes	T1, T2, T3, T4, T5, T6	attendance records and completion records
Exploratory outcomes		
arterial blood gas parameters	T0, T6	PaO₂ and PaCO₂
Traditional Chinese Medicine (TCM) Syndromes assessment	T0, T6	TCM Syndrome Scale
patient satisfaction	T6	patient satisfaction questionnaire
safety	T1, T2, T3, T4, T5, T6	adverse event records
Long-term follow-up outcome	Monthly during the 1-year post-intervention follow-up	Number of AECOPD

### Participants and recruitment

2.2

Recruitment for this trial will be conducted at four participating centers in China, including the Fifth Affiliated Hospital of Guangzhou Medical University, Anshun People’s Hospital, Xixiu District People’s Hospital of Anshun, and Pingba District People’s Hospital of Anshun. The study protocol has been approved by the Ethics Committees of all participating centers (Ethics Review Numbers: GYWY-L2024-96, ASSRMYYLL-20240168, 2025-EC-001, 20,250,014). Clinical staff at each subcenter will pre-screen and potential participants. To standardize procedures and advance recruitment efforts, the lead unit’s research team will hold monthly in-person or online meetings with all of the subcenter clinical members. Interested patients who meet preliminary criteria will be invited to the hospital. Researchers will provide an in-person study introduction and address patient inquiries.

Voluntarily participating patients will undergo further medical history interviews and pulmonary function tests to confirm final eligibility. After providing written informed consent, eligible patients will complete baseline assessments. The initial intervention must be administered within 14 days following the baseline assessment.

#### Inclusion criteria

2.2.1

Patients must meet all of the following criteria for enrollment:

Diagnosis of COPD according to the 2024 GOLD guidelines, defined as the presence of chronic respiratory symptoms (dyspnea, cough, sputum production) due to airway and/or alveolar abnormalities, and/or history of exposure to risk factors, with post-bronchodilator FEV_1_/FVC < 0.7. Disease severity is classified as: GOLD grade 1 (mild, FEV_1_ ≥ 80%), GOLD grade 2 (moderate, FEV_1_ 50–79%), GOLD grade 3 (severe, FEV_1_ 30–49%), and GOLD grade 4 (very severe, FEV_1_ < 30%). ① age 40–75 years; ② GOLD grades 2–4 (FEV_1_% ≤ 79%); ③ ability to walk independently; ④willingness to participate and provision of written informed consent after understanding the study purpose.

#### Exclusion criteria

2.2.2

Patients will be excluded if they meet any of the following criteria: ① acute exacerbation of COPD within the past 2 weeks; ② comorbid psychiatric disorders, cognitive impairment, severe neurological deficits (e.g., aphasia, agnosia), or severe hearing impairment that would preclude cooperation; ③ active tuberculosis, pulmonary fibrosis, pneumothorax, or lung cancer; ④ severe systemic diseases affecting cardiac, renal, hepatic, or muscular functions; ⑤ requirement for mechanical ventilation; ⑥ aversion to music; ⑦ participation in pulmonary rehabilitation programs within the past 12 months; or ⑧ current participation in other clinical trials.

### Randomization and blinding

2.3

This study employed a centralized randomization system with stratified randomization by research center and variable block lengths. A computer-generated random sequence assigned eligible participants in a 1:1 ratio to either the music therapy group or the conventional pulmonary rehabilitation group. Each stratum contained 3 to 10 participants per group to ensure balanced group sizes. To conceal allocation, assignments will be placed in sequentially numbered, opaque, tamper-evident envelopes. The site coordinator will open the envelope only after the participant completes consent and baseline assessments, immediately before the first session.

Due to the nature of the interventions, participants and therapists is not blinded, while staff responsible for outcome assessment and statistical analysis will be blinded.

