### Statistical analysis

2.7

All statistical analyses will be conducted in accordance with the pre-specified statistical analysis plan. The primary non-inferiority analysis will be performed simultaneously in both the intention-to-treat (ITT) and per-protocol (PP) populations.

The primary endpoint is the between-group difference change in 6MWD from baseline to week 6 (T6). The treatment effect difference will be defined as the mean change in 6MWD in the MTG minus that in the CPRG. The primary endpoint will be analyzed using a mixed model for repeated measures (MMRM), which will serve as the main confirmatory analytic approach. The model will incorporate 6MWD measurements at all pre-specified follow-up time points. Treatment group, visit time, the interaction term between group and time, study center, and baseline 6MWD will be treated as fixed effects. And an appropriate covariance structure will be used to account for the correlation of repeated measurements within participants.

Non-inferiority will be assessed based on the between-group difference in change from baseline in 6MWD at T6, as estimated by this model. If the lower limit of the two-sided 95% confidence interval for the treatment effect difference is greater than the pre-specified non-inferiority margin of −25 m, the music therapy group will be deemed non-inferior to the conventional pulmonary rehabilitation group.

Weekly repeated 6MWD measurements will also be used to support longitudinal analyses aimed at describing the trajectory of treatment effects over time; however, they will not serve as an additional confirmatory primary endpoint.

Missing data for the primary endpoint will be handled under a mixed-effects model framework based on the missing-at-random (MAR) assumption. Multiple imputation will be used as a prespecified sensitivity analysis to assess the robustness of the primary results.

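### The primary 6MWD model leaves out baseline FEV1 although entry spans GOLD 2 to 4 and FEV1 is measured at T0: a modest, nearly free gain in precision and robustness is given up

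*Protocol article*

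**What the plan says.** - **Eligibility** (Inclusion criteria, 2.2.1). Severity enters as "GOLD grades 2–4 (FEV_1_% ≤ 79" per cent, with no lower limit. By the article's own grading this takes in moderate, severe and very severe disease. The abstract is narrower in wording ("We plan to recruit 76 patients with stable moderate-to-severe COPD"). The two descriptions should be reconciled, but the point below does not depend on which is kept.
- **Allocation** (Randomization and blinding, 2.3). The only stratification factor named is the center: "This study employed a centralized randomization system with stratified randomization by research center and variable block lengths". There are four centers.
- **Primary model** (Statistical analysis, 2.7). The MMRM uses all weekly 6MWD values, and its terms are listed: "Treatment group, visit time, the interaction term between group and time, study center, and baseline 6MWD will be treated as fixed effects". Neither FEV1 nor GOLD grade is among them. Missing primary data are handled in this model under missing-at-random, with multiple imputation as a sensitivity analysis. Non-inferiority is assessed in both the ITT and PP populations.
- **Availability of a severity measure** (Study design, 2.1, and Table 1). "Pulmonary function and arterial blood gas analysis will be measured at T0 and T6".

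**The concern.** Six-week gain in walking distance, and whether a patient completes the program, may both depend on airflow limitation beyond what the starting walk distance shows. If so, a model without a severity term has two costs.

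1. **Precision.** Outcome variance that a baseline measurement could remove stays in the residual. The verdict rests on one confidence limit against -25 m, and the design has almost no power in reserve.
2. **Missing data and selection.** Missing-at-random must hold given arm, center, baseline 6MWD and the observed weekly walks only. Conditioning on less makes it a stronger assumption and a harder one to believe. The PP set raises a related issue: it is selected after randomization, so a severity difference between arms in that set could be systematic.

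The second cost has some footing in this trial. Section 2.7 relies on missing-at-random, section 2.8 plans for 20% dropout, and section 2.4 acknowledges that the arms differ in workload, so staying in the program could depend on severity differently in each arm.

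**Working it through.** **Inputs from section 2.8:** margin 25 m; SDs of change 36.6 and 32.3 m; one-sided alpha 0.025; power 80%; 30 evaluable per arm; 20% dropout; 38 randomized per arm. **Assumed, because the article gives none of them:** true difference 0; half the patients GOLD 3-4; these patients gain d = 10 to 20 m less; the dropout patterns in step 4.

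**1. The plan's own figure.** Mean variance = (36.6² + 32.3²)/2 = 1191.4 m², so SD = 34.52 m. n per arm = 2 × 1191.4 × (1.96 + 0.8416)² / 25² = 29.9, rounded up to 30. With dropout, 30/0.8 = 37.5, rounded up to 38. Both stated figures reproduce. SE at 30 per arm = 34.52 × √(2/30) = 8.91 m; power = Φ(25/8.91 − 1.96) = 80.1%.

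**2. Precision given up.** Share of variance due to severity: R² = p(1−p)d²/1191.4. Power after adjustment: Φ(25/(8.91√(1−R²)) − 1.96).

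| p (GOLD 3-4) | d | R² | Power at 30 per arm |
|---|---|---|---|
| 0.5 | 10 m | 25/1191.4 = 2.1% | 80.9% |
| 0.5 | 20 m | 100/1191.4 = 8.4% | 83.4% |

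With p = 0.3 the R² values are 21/1191.4 = 1.8% and 84/1191.4 = 7.1%. All are before overlap with baseline 6MWD, which can only reduce them. An R² of 10% would need d = √(0.10 × 1191.4/0.25) = 21.8 m, outside the assumed range. A simulation with 38 randomized per arm and 20% random dropout (6,000 runs) agrees: power went from 79.6% to 80.1% at d = 10 m and from 80.0% to 82.3% at d = 20 m.

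**3. Chance imbalance.** The SE of the between-arm difference in the GOLD 3-4 share at 38 per arm is √(2 × 0.25/38) = 11.5 points. A gap at the 95% limit (1.96 × 11.5 = 22.5 points) moves the contrast by 2.2 to 4.5 m. This is random error. In the simulation, one-sided type I error without a severity term was 2.5% to 2.7% when dropout was unrelated to severity, or related to it equally in both arms.

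**4. Dropout that depends on severity differently by arm.** Let severe and other patients drop out at 30% and 10% in the music arm. The severe share among its completers is 0.35/(0.35 + 0.45) = 43.75%.

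- Against 20% dropout for everyone in the control arm (severe share 50%), the difference is 6.25 points. Bias = 0.0625 × d = 0.6 to 1.25 m; simulated type I error 2.9% to 3.6%.
- Against the reversed pattern of 10% and 30% (severe share 56.25%), the difference is 12.5 points. Bias = 0.125 × d = 1.25 to 2.5 m; simulated type I error 3.7% to 5.0%.

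With severity in the model, type I error was 2.5% in both cases. In this direction the bias favors non-inferiority; if severe patients leave the control arm more often, it runs against the music arm. These are upper-end figures, because the simulation used neither baseline nor weekly 6MWD, both of which the planned MMRM uses.

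**5. Stratification as an alternative.** Four centers × three grades = 12 strata, or 38/12 = 3.2 patients per arm in each. That is not clearly better than stratifying by center alone.

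**The case against.** The strongest reply is that nothing here is wrong. The model adjusts for the stratification factor and for the baseline value of the endpoint, and baseline 6MWD may already carry part of the severity signal. Omitting a further prognostic covariate is a defensible prespecified choice. A typical imbalance is also small: a 15-point gap, which at 38 per arm arises in about 20% of trials in either direction, shifts the contrast by 1.5 to 3 m, or 0.17 to 0.34 of the 8.91 m SE. Every severity input is assumed. All of this stands, and it keeps the point to an improvement. It does not remove the case for a covariate that is already collected.

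A reader might infer more, and the documents do not support it:

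- **That chance severity imbalance biases the contrast or inflates type I error.** It does neither in the ITT comparison; step 3 shows the error rate held.
- **That randomization should have been stratified by severity.** Step 5 gives no support for this at 76 participants.
- **That any link between dropout and severity breaks the analysis.** It does harm only if severity predicts the missing week-6 walk beyond center, baseline and observed weekly walks and, for the between-arm contrast, mainly if the pattern differs by arm. The article gives no dropout by severity or arm.
- **That the ITT analysis rests on about 30 per arm.** That is the evaluable number in the sample-size calculation. In the MMRM, a participant who leaves after T1 still contributes.
- **That the imputation model omits FEV1.** Its variables are not listed, and that detail properly belongs in the SAP.

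**Conclusion.** The point holds as a low-cost improvement to a stated model, not as an error. The primary analysis is valid without it. On the assumptions of a 10 to 20 m severity effect and half the sample GOLD 3-4, the gain is about 1 to 3 percentage points of power at 30 per arm, and less to the extent that baseline 6MWD already carries the severity signal. Protection against arm-specific, severity-related dropout or PP exclusion is worth at most about 0.6 to 2.5 m against a 25 m margin, under assumed patterns that ignore baseline and weekly 6MWD. If the SAP, which is not shown, already includes baseline FEV1, only the term list in section 2.7 needs to be aligned with it.

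**What to change.** In section 2.7 and the SAP, add baseline FEV1 % predicted, taken from the T0 spirometry and entered as a continuous variable, as a prespecified fixed effect in the primary MMRM for both the ITT and PP analyses. Settle this before unblinding, since a covariate added later would look data-driven. Keep randomization as it is.

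The cost is one line of text and one model degree of freedom, with no new data and no larger sample. The only downside is a very slight loss of precision if FEV1 proves unrelated to 6MWD change.

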### Interventions

2.4

All participants will continue their stable, regular pharmacotherapy, throughout the study, including prescribed bronchodilators and/or inhaled corticosteroids. Prior to the first treatment session, all participants will receive standardized instruction on diaphragmatic breathing and pursed-lip breathing to ensure that all groups performed these basic techniques safely and consistently. Both groups will receive treatment three 60-min sessions per week for 6 weeks. Detailed information regarding the intervention protocol, therapist training, competency requirements, progression criteria, and adherence monitoring is provided in the Supplementary material.

The Music Therapy Group (MTG) will receive a structured intervention that combines music-guided breathing exercises with singing, administered by a trained therapist following a standardized protocol. The intervention is designed to promote participants’ active control of inspiratory and expiratory muscles through coordinated breathing, voice training, and singing. Each session includs a brief introduction and status check (2 min), health education (3 min), rhythm-guided breathing training (20 min), vocalization training (10 min), and singing (25 min). Participants will first complete diaphragmatic and pursed-lip breathing exercises synchronized with a standardized piano rhythm, followed by vocalization and singing tasks. The standardized song repertoire will be selected based on principles such as steady rhythm, moderate phrase length, comfortable vocal range, and cultural familiarity. The singing sessions will progress from easy to difficult levels according to the respiratory tolerance and control performance of participants. Training intensity will be maintained within symptom-tolerable limits and monitored using the modified Borg dyspnea scale, heart rate, and peripheral oxygen saturation.

The Conventional Pulmonary Rehabilitation Group (CPRG) will receive conventional pulmonary rehabilitation interventions administered by a trained therapist following a standardized protocol. The CPRG will be matched with the MTG in terms of total intervention duration and therapist contact time. Each session will include a brief introduction and status check (2 min), health education (3 min), breathing exercises (20 min), and exercise training (35 min). Breathing exercises will include diaphragmatic breathing and pursed-lip breathing under the therapist’s guidance. Exercise training will take place in a music-free environment and include breathing exercises and the Eight Brocades. The progression of intensity and methods of physiological monitoring will be consistent with those in the MTG, but will not include any music-related therapeutic components.

The two groups were consistent in terms of intervention frequency, session duration, therapist contact time, and progress monitoring frameworks, but differed in their workload designs. The intervention group utilized rhythm-guided breathing exercises, vocalization exercises, and singing, while the control group employed breathing exercises combined with standardized exercise training. Consequently, this music-guided program was regarded as an alternative rehabilitation model rather than a supplement to traditional pulmonary rehabilitation.

To ensure consistency in the implementation of the intervention across all research centers, all therapists will undergo standardized training prior to participant enrollment. The intervention will be implemented in accordance with the protocol manual and session checklists, and the research team will periodically review protocol adherence and any deviations in implementation.

